  1. SECONDARY DATA ANALYSES

**Utilization of healthcare services overall and per subgroups based on claims data**

- Outpatient care data: average frequency (days, cases) of outpatient practitioner visits by specialty, with average costs per case, visit, and overall costs per patient-year, pre- and post-intervention time.
- Prescriptions of medications: number of outpatient prescriptions of medications with average daily doses per therapeutic area (as per ATC classification), overall costs per patient-year, pre- and post-intervention.
- Allied health professions (podiatric, dietary, speech and language, occupational and physiotherapy): average amount/duration of prescribed remedies per diagnosis group, cardinal symptom and remedy type per patient-year, pre- and post-intervention.
- Assistive technology prescription: frequency of prescription of assistive and therapeutic appliances per product group and patient-year, pre- and post-intervention.
- Inpatient hospital stays: number, duration, average cost of inpatient hospital stays per leading diagnosis and patient-year, pre- and post-intervention.
- Outpatient hospital care: number, duration, average costs of outpatient hospital care per leading diagnosis and patient-year, pre- and post-intervention.
- Work incapacitations: number and duration of work incapacitation per ICD-10-GM main groups and patient-year, pre- and post-intervention.
- Transportation costs: frequency, duration, and type of transportation, average costs per patient-year, pre- and post-intervention
- Household assistance: frequency, duration, type of assistance, and average costs per patient-year, pre- and post-intervention
- Nursing care: frequency, duration, type of care, and average costs per patient-year, pre- and post-intervention
- Rehabilitation: frequency, duration, type of rehabilitation, and average costs per patient-year, pre- and post-intervention
- Long-term care benefits: highest level of care, frequency, duration, type of care, and average costs per patient-year, pre- and post-intervention

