   1. STUDY DESIGN

The study is an observational prospective cohort study with patients of four chronic disease areas with existing DMPs (asthma, chronic obstructive pulmonary disease (COPD), diabetes (type 1 and type 2) and coronary artery disease) with two sub-cohorts (DMP and non-DMP) for each disease.

- Type of control: none / group matched BARMER insurees (matching criteria: disease area, gender, age group)
- Level and method of blinding: none
- Method of treatment assignment: stratified randomized selection of study population
- Number of subjects: 200,000 patients invited (50,000 per chronic indication and about 25,000 in each sub-cohort)
- Duration of study: one year (four quarterly survey periods)

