  1. STUDY POPULATION

Inclusion criteria:

- Patient is at least 18 years old
- At least two outpatient consultations documenting a confirmed chronic disease diagnosis in 2021
- For type 1 diabetes at least one insulin prescription must be present in 2021

Exclusion criteria:

- Participation in more than one DMP

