  1. INTERVENTION

In addition to filling out the survey questions at four points in time (intervention 1), all participants will receive PRO feedback as a potential nudge (intervention 2). The PRO feedback will be a pdf report sent via email and available in their study participant profile, which graphically (line charts) shows the patients’ individual generic and disease-specific health status in comparison to the individual peer group. In addition to the visual feedback, the results will shortly be explained on the same page. The description will cover whether patient-individual PRO scores are better or worse compared to the peer group, and for longitudinal values, whether patient-related changes improved or worsened. Additional details on the scores, sub-scores, and calculations are shared with the patients on the following pages of the report. Peer groups are classified according to their disease, gender, and age group. The peer group is created based on individuals who have replied to the previous survey and will only be displayed if the group consists of at least four individuals. This threshold is set by the German General Data Protection Regulation. The report refers to the patients’ physicians as the main contact to discuss the results or in case of questions.

- 1. SAMPLE SIZE

The sample is drawn stratified randomly from insured patients of one large German statutory health insurance with about 9 million insured persons (of about 73 million statutorily insured persons in total in Germany) according to their diagnosis and/or disease management program status. A one-to-one matching of participants of one DMP with non-participants of a DMP but with the same proven diagnosis according to the ICD-10-GM system is made. Further stratification criteria are age group, gender, and health system utilization.

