- Using machine learning predictive models (long-short-term memory deep learning network for time trend classification, random forest, logistic regression, decision tree and/or support vector machine) to identify admission risk in Q3 and Q4 based on PROMs/PREMs in Q1 and Q2

*PRO feedback*

- Mainly: Statistically significant change in at least one of the health care behavior dimensions (see 4.2) and comparison of participants who opened the report vs. those who did not, using logistic regression (change/no change)
  - Physical activity: Shift of participants to a higher category
  - Nutrition: Shift of participants to “More healthy” from any other category
  - Tobacco: Shift of participants to a lower category
  - Alcohol: Shift of participants to a lower category
  - Sleep: Share of stable participants (no significant variation in sleep duration)
- Secondly: Descriptive exploratory analysis of the rates of the following two evaluation dimensions and statistically significant differences in subgroups (see 5.1 and 4.3):
  - Understandability
  - Helpfulness
  - Emotional change

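### Section 5.3 reports every claims outcome as a pre/post change with no comparator, so calendar trends cannot be separated from the feedback; a pre window that includes 2021 would add regression to the mean

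*Protocol*

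**What the plan says.** Section 5.3 carries the title "Utilization of healthcare services overall and per subgroups based on claims data" and lists twelve domains, from outpatient care to long-term care benefits. Each is to be given before and after the intervention, as in "overall costs per patient-year, pre- and post-intervention time". The section names no comparator, model, time window or adjustment for calendar time.

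Four other places bear on this:

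- Section 2.4: "all participants will receive PRO feedback as a potential nudge (intervention 2". No participant goes without feedback by design.
- Section 2.1: "Type of control: none / group matched BARMER insurees (matching criteria: disease area, gender, age group". The entry gives both no control and a matched control, and section 5.3 does not take up either.
- Section 2.3: entry requires "At least two outpatient consultations documenting a confirmed chronic disease diagnosis in 2021", and "For type 1 diabetes at least one insulin prescription must be present in 2021".
- Section 3 defines the analysis population as selected patients who took part, less those who withdraw consent, and applies it to all analyses.

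Section 4.1 states that utilization data exist for the insurer's whole population as well as for participants.

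**The concern.** A before/after change in an exposed group contains any effect of the feedback plus everything else that moved over the same period: fee schedules, supply of care, ageing and progression of chronic disease. Without a concurrent unexposed group these parts cannot be told apart, in any of the twelve domains.

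The entry rule adds a second, conditional problem. People are chosen because their 2021 count of diagnosis-related consultations was at least two. If 2021 serves as the pre period, its mean is raised by selection and the later mean is not. Visits then fall even if nobody changes.

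The second objective asks whether feedback leads patients to approach their physicians more actively. A spurious fall in outpatient visits could hide such an increase or be taken for a saving. A calendar trend could push either way.

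**Working it through.** **1. Is there a comparator for section 5.3?**

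| Place | Comparison offered | Unexposed to feedback? | Used in 5.3? |
|---|---|---|---|
| 2.1 | none, or matched insurees (disease area, gender, age group) | yes, if chosen | not mentioned |
| 5.1 | DMP vs non-DMP | no, both receive it | not as a control |
| 5.2, PRO feedback | report opened vs not opened, for health behaviour | no, self-selected | not mentioned |
| 5.2, data analysis | responders vs non-responders to the nudge | no, self-selected | not mentioned |

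Only section 2.1 offers an unexposed group. It leaves the choice open, and section 3, read literally, shuts that group out.

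**2. Expected size.** 200,000 × 0.30 × 2/3 × 0.40 = 16,000, which reproduces the protocol's figure for complete data sets. The protocol gives no effect size, standard deviation or power for section 5.3.

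**3. How small a shift would count as significant?** Section 5.1 uses two-sided 0.05. For a paired mean change the threshold is 1.96 × CV / √n, where CV is the standard deviation of the change divided by the baseline mean (assumed 1 to 3).

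- n = 16,000: 1.96 × 1 / 126.5 = 1.5%, up to 4.6% at CV 3.
- n = 4,000 (one disease of four): 3.1% to 9.3%.

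If these changes were tested, a calendar shift of a few per cent would suffice.

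**4. Regression to the mean if 2021 is the pre year.** Assume a stable personal rate, gamma distributed with mean m and shape k, Poisson counts in each year, and no true change. Then

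- P(0) = (k/(k+m))^k and P(1) = k × m/(k+m) × P(0)
- pre mean = (m − P(1)) / (1 − P(0) − P(1))
- post mean = (k + pre mean) / (k/m + 1)

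Example with m = 4, k = 2: P(0) = 0.111, P(1) = 0.148, pre = 3.852/0.741 = 5.20, post = 7.20/1.5 = 4.80, change −7.7%.

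| Mean per year | k = 1 | k = 2 | k = 4 |
|---|---|---|---|
| 2 | −16.7% | −21.4% | −25.3% |
| 4 | −6.7% | −7.7% | −8.1% |
| 6 | −3.6% | −3.6% | −3.1% |
| 8 | −2.2% | −1.9% | −1.4% |

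Under the same model, a pre window that excludes 2021 gives a change of about zero. Means and shapes are assumptions, as the protocol gives neither.

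**5. Should a comparator be matched on 2021 utilization?** Assume k = 2, participants' mean 4, comparators' mean 6, no effect, and both groups selected on at least two visits in 2021.

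- Same entry rule, no matching on the count: participants 5.20 → 4.80 (−0.40); comparators 7.00 → 6.75 (−0.25). Difference −0.15.
- Matched on the 2021 count: comparators start at 5.20 and move to (2 + 5.20)/(2/6 + 1) = 5.40 (+0.20). Difference −0.40 − 0.20 = −0.60, or −11.5% of 5.20.

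Matching on the baseline count makes each group regress to its own mean and enlarges the artefact.

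**The case against.** The strongest reply is that section 5.3 is a list of descriptive averages. It states no hypothesis or causal test. The study is declared observational, and the feedback outcomes in sections 4.2 and 5.2 are comprehensibility, helpfulness and health behaviour, not claims. A reader might infer that the sponsor will judge the feedback by these before/after figures and that an artefact will be reported as its effect. The text does not say so. What it does is label the periods by the intervention and name the feedback as a nudge, which invites that reading without stating it.

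A reader might also carry the 17-25% over to every claims outcome. That is not supported. It needs 2021 as the pre window and a mean of about two diagnosis-related visits per year. The entry rule acts directly only on those visits and, in type 1 diabetes, on insulin prescriptions. Visits for any reason, hospital stays, work incapacity and the other domains are affected less. The sample is also stratified on utilization, which the simple model ignores.

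It may further be said that windows and the use of a named comparator belong in a statistical analysis plan. That is fair for detail. It does not cover a control given as both absent and present, or a rule that keeps non-participants out of every analysis. That rule already sits badly with section 4.1, whose primary comparison needs data on the whole target population. The internal comparisons in section 5.2, such as "comparison of participants who opened the report vs. those who did not, using logistic regression (change/no change", do not fill the gap, because patients sort themselves into those groups.

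**Conclusion.** The point holds in a limited form. As written, section 5.3 cannot separate calendar trend from the feedback in any of its twelve domains, and this does not depend on where the windows fall. The size of any trend cannot be computed from the protocol. At 16,000 participants a change of 1.5% to 4.6% would reach the 0.05 level under an assumed CV of change of 1 to 3.

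Regression to the mean is conditional on the pre window including 2021. It then lowers later diagnosis-related visits by 17-25%, 7-8% or 1-2% at assumed means of 2, 4 or 8 per year. The same mechanism acts on insulin prescriptions in type 1 diabetes, where its size was not computed. If the window excludes 2021 it is about zero, given stable personal rates.

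The matched group in section 2.1 would help with calendar trend. It would not necessarily remove regression to the mean, because its members are not said to meet the 2021 entry rule, and DMP status is not among its matching criteria.

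**What to change.** - **Section 2.1:** replace the open entry with a firm comparator: insurees who meet the same 2021 entry criteria, matched or weighted on disease, DMP status, age group and gender.
- **Section 3:** exempt section 5.3 from the participants-only rule.
- **Section 5.3:** define the pre and post windows, with the pre window separate from the 2021 selection year. Report the participant-minus-comparator difference in change (difference-in-differences) with person-clustered standard errors.
- **Matching:** do not match on utilization measured in the period that serves as the baseline, since this can itself create regression to the mean.
- **Labelling:** call within-participant pre/post figures descriptive only.

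The cost is wording and one further claims extract, from data that section 4.1 says are available. Participants remain volunteers who chose to respond, which a comparator drawn from claims does not remove. The protocol should state this as a limitation.
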